# Comparative Outcomes of a Pediatric Walking Rehabilitation Robot Combined With Repetitive Transcranial Magnetic Stimulation in Children With Spastic Cerebral Palsy: Protocol for a Prospective Observational Study

**DOI:** 10.2196/93798

**Published:** 2026-06-29

**Keywords:** cerebral palsy, CP, rehabilitation robot, repetitive transcranial magnetic stimulation, rTMS, rehabilitation medicine

## Abstract

**Background:**

Cerebral palsy (CP) is a prevalent neurodevelopmental disorder in children, often leading to long-term motor impairments. Rehabilitation robotics has emerged as a promising approach in pediatric neurorehabilitation, offering precise and repetitive motor training. Repetitive transcranial magnetic stimulation (rTMS), a noninvasive neuromodulation technique, has shown potential in modulating cortical excitability and improving motor function in children with CP.

**Objective:**

This study aims to evaluate the association between a combined intervention using a pediatric gait rehabilitation robot and rTMS in children with spastic CP.

**Methods:**

This prospective observational study will enroll 108 children with spastic CP who meet the inclusion criteria. Participants will be allocated to either an intervention group (robot-assisted gait training combined with rTMS) or a comparison group (conventional rehabilitation therapy) based on their guardians’ preference after standardized information provision. The assignment is nonrandomized and will be documented prospectively. Interventions will be delivered 5 times per week for 8 weeks. Outcomes will be assessed at baseline, week 4, and week 8 using 3D gait analysis, neuromuscular electromyography, the Gross Motor Function Measure-88, and the Modified Ashworth Scale. Comparative analyses will be conducted to evaluate the outcomes of the combined intervention relative to standard rehabilitation. Findings are expected to provide evidence supporting integrated neuromodulation and robotic therapy in pediatric CP rehabilitation.

**Results:**

This study was funded in 2024. Study recruitment began in January 2025, and as of June 2026, enrollment is ongoing; exact recruitment numbers are being verified with the research coordinator. This study has been approved by the ethics committee (YJ-2025-020-01) and supported by grants S2024094 and CDS2018Z005. Outcomes will be assessed at baseline, week 4, and week 8 via 3D gait analysis, electromyography, Gross Motor Function Measure-88, Modified Ashworth Scale. Data collection is expected to be complete in December 2027, and the data will be analyzed with SPSS. The results are expected to be published in spring 2028.

**Conclusions:**

This study evaluates the comparative outcomes associated with a pediatric gait rehabilitation robot combined with rTMS for children with spastic CP. Positive findings would suggest a preliminary association between the multimodal protocol and better motor function (including improved gait performance and reduced muscle spasticity), without implying causality. Such results would provide a new evidence-based option for pediatric spastic CP rehabilitation.

**Trial Registration:**

Chinese Clinical Trial Registry ChiCTR2500105823; https://www.chictr.org.cn/showproj.html?proj=274950

**International Registered Report Identifier (IRRID):**

DERR1-10.2196/93798

## Introduction

### Background

Cerebral palsy (CP) is one of the most common neurodevelopmental disorders in children and is characterized by permanent motor impairment resulting from nonprogressive injury to the developing brain. Epidemiological studies indicate that the prevalence of CP among children aged 1 to 6 years is approximately 2.46% in China and ranges from 0.14% to 0.32% globally [1]. Spastic CP, the predominant subtype, accounts for nearly 70% of cases [2,3]. It is characterized by hypertonia and hyperreflexia, often leading to abnormal posture and gait patterns, including limb spasticity, flexor dominance, trunk flexion, knee flexion, and scissor gait. These motor impairments frequently persist throughout childhood and may evolve with growth and development, substantially affecting functional independence and quality of life.

The pathophysiology of spastic CP is complex and multifactorial, involving cortical and subcortical injury, impaired neurodevelopment, and secondary musculoskeletal abnormalities [4]. A widely recognized mechanism is the disruption of supraspinal regulation of spinal stretch reflexes following central nervous system injury, resulting in exaggerated reflex excitability and increased muscle tone [5,6]. Current rehabilitation strategies are typically multimodal and include physical therapy, occupational therapy, pharmacological management, orthopedic surgery, and complementary approaches, such as traditional Chinese medicine. Despite these interventions, functional recovery remains challenging, particularly in children with moderate-to-severe motor impairments. Consequently, there is growing interest in innovative rehabilitation approaches capable of promoting neuroplasticity and improving motor outcomes.

Among these emerging interventions, repetitive transcranial magnetic stimulation (rTMS) has gained increasing attention as a noninvasive neuromodulation technique. By delivering pulsed magnetic stimulation to targeted cortical regions, rTMS can modulate neuronal excitability and facilitate neuroplastic reorganization [7]. Previous studies have demonstrated its therapeutic potential in various neurological and neuropsychiatric disorders, including stroke, anxiety, depression, and, increasingly, CP [8-12]. Mechanistically, rTMS is believed to regulate synaptic plasticity, restore interhemispheric balance, and enhance corticospinal tract function, particularly when applied to the primary motor cortex. Importantly, rTMS is generally well tolerated in pediatric populations and allows relatively precise cortical targeting. A recent meta-analysis of 16 randomized controlled trials reported that rTMS was associated with improvements in gross motor function (Gross Motor Function Measure [GMFM]; standardized mean difference [SMD] 0.47-0.63) and gait velocity (SMD 1.28) in children with CP [13]. Nevertheless, the optimal stimulation protocols and their integration with rehabilitation training remain insufficiently established.

Parallel to developments in neuromodulation, rehabilitation robotics has emerged as a promising technology in pediatric neurorehabilitation. Robotic systems can incorporate real-time monitoring, adaptive algorithms, and task-oriented training environments to deliver intensive, repetitive, and individualized motor rehabilitation [14,15]. Compared with conventional therapy, robot-assisted interventions offer improved movement reproducibility, precise control of training parameters, and enhanced feedback mechanisms that may facilitate motor learning. In this study, we used a pediatric gait rehabilitation robot (BFR-K-A200; Chengdu Buffalo Robotics Technology Company), which combines an exoskeleton with a wheeled walker to assist in standing, walking, and lower-limb coordination. This device provides active and passive joint assistance and may improve gait efficiency and training adaptability compared with conventional exoskeleton-based systems.

Although both robotic gait training and rTMS have demonstrated potential benefits individually, evidence regarding their combined application in pediatric spastic CP remains limited. Given their complementary therapeutic mechanisms—robot-assisted training targeting peripheral motor execution and gait relearning, and rTMS targeting central neuromodulation and cortical plasticity—their integration may produce synergistic rehabilitation effects. Therefore, this prospective observational study aims to evaluate the clinical outcomes associated with robot-assisted gait training combined with rTMS in children with spastic CP. Treatment effects will be assessed using 3D gait analysis, neuromuscular electromyography, the GMFM-88, and the Modified Ashworth Scale (MAS), with the goal of generating evidence to inform multimodal and evidence-based rehabilitation strategies for this population.

### Study Objective and Hypothesis

The primary objective of this study is to evaluate the clinical outcomes associated with a pediatric gait rehabilitation robot combined with rTMS in adolescents with spastic CP, compared with conventional rehabilitation therapy.

The primary hypothesis is that participants receiving robot-assisted gait training combined with rTMS may show greater improvements in gross motor function, gait performance, and muscle tone than those receiving conventional rehabilitation after 8 weeks of intervention. However, due to the observational design, causal inference is not possible. Specifically, changes in GMFM-88 scores from baseline to week 8 will serve as the primary end point. Secondary hypotheses are that the intervention group will exhibit superior improvements in 3D gait parameters, electromyography outcomes, and MAS scores at weeks 4 and 8.

Given the observational nature of the study, any observed between-group differences will be interpreted as associations rather than causal effects.

## Methods

### Study Design

This study is designed as a prospective observational controlled study to evaluate the clinical outcomes associated with robotic gait training combined with rTMS in adolescents with spastic CP. An observational design was selected primarily because treatment allocation is influenced by family preference and clinical decision-making in real-world rehabilitation settings. In addition, the highly visible and technology-intensive nature of robotic rehabilitation limits the feasibility of participant and therapist blinding. Nevertheless, to minimize assessment bias, outcome evaluations will be conducted by independent rehabilitation physicians who are not involved in treatment delivery and are blinded to group allocation whenever feasible.

Eligible participants will be allocated to either an intervention group (robot-assisted gait training combined with rTMS) or a comparison group (conventional rehabilitation therapy) according to guardian preference after receiving standardized study information from a neutral research coordinator who is not involved in treatment administration or outcome assessment. Allocation decisions will be prospectively documented, and no randomization will be performed. Both groups will receive 5 treatment sessions per week over an 8-week intervention period. Clinical evaluations will be performed at baseline, week 4, and week 8 by trained rehabilitation physicians using standardized assessment procedures. The study flowchart is presented in Figure 1, and the schedule of enrollment, intervention, and assessment is summarized in Figure 2. This protocol was developed in accordance with the SPIRIT (Standard Protocol Items: Recommendations for Interventional Trials) guidelines and will be reported following the STROBE (Strengthening the Reporting of Observational Studies in Epidemiology) statement for observational studies [16,17]. Participant recruitment is scheduled to commence in January 2025, with data collection anticipated to be completed by December 2027.

**Figure 1 figure1:**
[figure not shown]
Flowchart. CP: Cerebral palsy; rTMS: repetitive transcranial magnetic stimulation.

**Figure 2 figure2:**
[figure not shown]
Schedule of enrollment, intervention, and assessment.

### Participants

A total of 108 adolescents with spastic CP will be recruited from the outpatient clinic of the Department of Rehabilitation Medicine, China National Nuclear Corporation 416 Hospital. The department is a tertiary rehabilitation center providing integrated clinical, teaching, and research services with extensive experience in pediatric neurodevelopmental disorder rehabilitation.

A structured summary of all eligibility criteria is presented in Textbox 1. Inclusion criteria define the target population, while exclusion criteria identify conditions that may confound outcome interpretation or pose safety risks.

Inclusion and exclusion criteria.
**Inclusion criteria**
Diagnosis of spastic cerebral palsy according to established clinical diagnostic criteriaAged between 13 and 18 yearsGross Motor Function Classification System levels I-VMedically stable and able to participate in rehabilitation trainingWritten informed consent provided by participants and/or legal guardians
**Exclusion criteria**
Severe epilepsy or uncontrolled seizure disorderSevere structural brain abnormalities or progressive neurological diseaseSevere cognitive or behavioral impairment precluding cooperationOther serious medical conditions compromising safety or participation

### Patient and Public Involvement

Patients and the public were not involved in the design, conduct, reporting, or dissemination plans of this study because of the technical and methodological complexity of the intervention protocol.

### Criteria for Withdrawal

Participants may be withdrawn from the study under the following circumstances:

Voluntary withdrawal of consent by participants or legal guardiansMajor protocol deviation or persistent noncomplianceAttendance below 80% of scheduled intervention sessionsInability to complete key outcome assessmentsOccurrence of serious adverse events or medical complications requiring discontinuationInvestigator judgment that continued participation may compromise participant safety or data integrity.

All withdrawals and reasons for discontinuation will be prospectively documented.

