#### Comparison Group

Participants allocated to the comparison group will receive conventional rehabilitation therapy, including resistance stretching, joint mobility training, balance training, core stability exercises, and functional electrical stimulation. Each session will last approximately 120 minutes and be delivered once daily, 5 days per week.

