#### Pediatric Gait Rehabilitation Robot

Robot-assisted gait training will be delivered using the pediatric gait rehabilitation robot (BFR-K-A200; Chengdu Buffalo Robotics Technology Co). This device integrates an exoskeleton with a wheeled walker and incorporates adaptive gait assistance algorithms informed by individualized movement characteristics.

Each robot-assisted training session will last 30 minutes. Participants in the intervention group will receive 2 sessions per day (one in the morning and one in the afternoon), 5 days per week, for a total of 8 weeks (ie, 80 sessions). The total daily intervention time for robot-assisted training is 60 minutes. Training intensity and gait assistance parameters will be individualized according to participant tolerance and rehabilitation needs.

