#### Concomitant Therapies

During the 8-week intervention period, participants in both groups will be asked not to receive any rehabilitation therapies outside the study protocol, as this would confound outcome interpretation. Any deviation from this requirement will be prospectively documented. Participants who receive substantial additional therapies (eg, more than 3 sessions) will be excluded from the per-protocol analysis but retained in the intention-to-treat analysis.

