#### Safety Monitoring

Safety procedures will be implemented throughout all interventions, including joint screening, warm-up and cooldown exercises, equipment inspection, and continuous monitoring for adverse reactions.

Children with contraindications to rTMS will be excluded prior to treatment initiation. To monitor fatigue associated with repeated training sessions, the pediatric OMNI Rating of Perceived Exertion scale (0-10) will be administered before each intervention session. Treatment intensity will be modified or sessions postponed if participants report perceived exertion scores ≥7.

All adverse events, including skin irritation, pain, dizziness, nausea, falls, muscle twitching, or seizures, will be recorded using standardized case report forms. Serious adverse events will be reported to the institutional ethics committee within 24 hours and will prompt immediate clinical evaluation and consideration of treatment discontinuation.

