#### Treatment Adherence Monitoring

Treatment adherence will be monitored throughout the 8-week intervention period using standardized attendance logs maintained by treating therapists. Attendance will be recorded at each scheduled treatment session and reviewed weekly by the study coordinator.

Adherence will be calculated as the proportion of completed sessions relative to the total number of scheduled sessions. Participants who attend less than 80% of the prescribed intervention sessions will be considered nonadherent and excluded from the per-protocol analysis but retained in the intention-to-treat analysis.

Any missed sessions, reasons for absence, and deviations from the intervention protocol will be documented prospectively. To enhance adherence, guardians will receive regular reminders and appointment confirmations during the study period.

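### Low attendance may lead to withdrawal from the whole study, although the treatment-policy estimand needs those participants' week-8 scores (minor)

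*Protocol article*

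**What the plan says.** All references are to the protocol article.

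- **Criteria for Withdrawal:** "Participants may be withdrawn from the study under the following circumstances". The list includes attendance under 80%, major deviation or persistent noncompliance, and serious adverse events or complications that require discontinuation. It does not separate stopping treatment from leaving the study. It also states "All withdrawals and reasons for discontinuation will be prospectively documented".
- **Treatment Adherence Monitoring:** participants below 80% "will be considered nonadherent and excluded from the per-protocol analysis but retained in the intention-to-treat analysis". The measure is defined: "Adherence will be calculated as the proportion of completed sessions relative to the total number of scheduled sessions". The study coordinator reviews attendance weekly.
- **Sensitivity Analyses:** the same 80% threshold is a per-protocol exclusion.
- **Concomitant Therapies:** a parallel rule covers outside therapy, "Participants who receive substantial additional therapies (eg, more than 3 sessions) will be excluded from the per-protocol analysis", again with retention in intention-to-treat.
- **Safety Monitoring:** serious adverse events "will prompt immediate clinical evaluation and consideration of treatment discontinuation". This concerns treatment, not follow-up.
- **Primary Estimand:** the group difference in GMFM-88 change from baseline to week 8, under a treatment-policy strategy.
- **Missing Data Assumptions and Handling:** the primary analysis covers everyone enrolled who has baseline data. Missing outcomes are multiply imputed (20 datasets) under missing at random, with complete-case analysis as a sensitivity check.

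**The concern.** One threshold has two consequences. One section lets the investigator end study participation; two others treat the same event as a matter for the per-protocol set and expect the participant to count in the main analysis. Under a treatment-policy estimand, poor attendance is an intercurrent event to be followed through, so the week-8 score after it is part of the target.

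Withdrawn participants do not leave the analysis set, because imputation fills their scores. What is lost is the measurement. If low attenders do less well than those who stayed, imputation informed mainly by the stayers overstates their result, and the group difference is biased when one group loses more of them.

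The planned checks would not reveal this. Complete-case analysis omits these participants, and per-protocol analysis excludes low attenders by rule. The inverse-probability weights model the choice of treatment, not withdrawal.

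**Working it through.** **1. The plan's own figures.** Sample Size Estimation assumes d = 0.60, two-sided alpha .05 and 80% power, and states 46 per group. A two-sample t-test calculation gives 44.6, so 45; power at 46 is 0.812. The stated 46 is close enough. For attrition, 46/0.85 = 54.1 against a stated 54, and 54 × 0.85 = 45.9. The allowance therefore covers about 8 losses of 54 per group. Power from 54 per group is 0.871 with no loss and 0.812 with 15% loss, so the question is bias rather than power.

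**2. When the threshold is crossed.** In the comparison group, "Each session will last approximately 120 minutes and be delivered once daily, 5 days per week" gives 5 × 8 = 40 sessions. Below 80% means fewer than 32 completed, which is certain at the 9th miss. For the robot, "5 days per week, for a total of 8 weeks (ie, 80 sessions" means fewer than 64 completed, certain at the 17th miss.

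| Attendance, evenly spread | Comparison (1 per day) | Robot (2 per day) |
|---|---|---|
| 75% (every 4th missed) | session 36, day 36, week 8 | session 68, day 34, week 7 |
| 50% (every 2nd missed) | session 18, day 18, week 4 | session 34, day 17, week 4 |

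The article does not say whether rTMS sessions also count. If all 160 robot and rTMS sessions count (4 per day), below 80% means fewer than 128 completed. The 33rd miss is then certain at session 132 with 75% attendance, which is day 33 and still week 7.

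The weekly review day is not stated. Assume that it is the last treatment day of the week and that the assessments fall on days 20 and 40. At 75% attendance, crossings on days 34 and 36 are reviewed on days 35 and 40, which is 5 and 0 treatment days before the week-8 assessment. At 50% attendance, both crossings are reviewed on day 20, when the week-4 assessment is due. Mainly the week-8 score is at risk.

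**3. Size of the bias.** The documents give neither withdrawals by ground nor the shortfall, so these figures are illustrative. Let w be the excess share withdrawn in one group, s their shortfall in SD against what would be imputed, and r the correlation between week 4 and week 8.

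- No week-4 score: bias = w × s.
- Week-4 score used, with half the shortfall already visible: bias = w × (s − r × s/2). Here r = 0.6 is assumed.

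| Excess of 54 | s = 0.30, no week 4 | s = 0.30, week 4 | s = 0.60, no week 4 | s = 0.60, week 4 |
|---|---|---|---|---|
| 3 | 0.017 | 0.012 | 0.033 | 0.023 |
| 4 | 0.022 | 0.016 | 0.044 | 0.031 |
| 8 | 0.044 | 0.031 | 0.089 | 0.062 |

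For example, 8/54 × (0.60 − 0.6 × 0.30) = 0.148 × 0.42 = 0.062. In that cell, r = 0.4 gives 0.071 and r = 0.8 gives 0.053.

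**4. Effect on inference.** SE = sqrt(2/54) = 0.192 SD. With z = bias/SE, coverage of a 95% interval is Phi(1.96 − z) − Phi(−1.96 − z).

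- Bias 0.022: coverage 94.9%.
- Bias 0.044: coverage 94.4%.
- Bias 0.089: coverage 92.5%. This bias is 0.089/0.60 = 15% of the assumed effect.

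**5. Would the planned checks show it?** Simulation with 3000 runs, 54 per group, 20 imputations and a true effect of 0.60 in those who stay:

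| Scenario | All scores collected | Complete case | Imputation |
|---|---|---|---|
| 8 withdrawn, s = 0.60, no week 4 | 0.51 | 0.60 | 0.60 |
| 8 withdrawn, s = 0.60, week 4 used | 0.51 | 0.60 | 0.57 |
| 4 withdrawn, s = 0.30, week 4 used | 0.575 | 0.597 | 0.590 |

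Complete-case and imputed results lie close together and both exceed the estimate from full follow-up. Their agreement would look reassuring when it should not.

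**The case against.** The best defence is that the withdrawal rule is permissive, while retention in intention-to-treat is stated without qualification. One governs participation and the other the analysis set, so both can be obeyed at once. That stands: the text permits loss of data and does not require it. A reader might infer that low attenders are dropped from the primary analysis. The documents do not support this, because imputation keeps them in the set.

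A second defence is that an article may leave follow-up after withdrawal to the full protocol. That would answer a complaint about silence. The point here rests on what is printed, namely that withdrawal is from the study. No analysis plan can recover scores that were never collected.

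A third is that attendance is reviewed weekly, so a decision may come too late to lose much. This stands in part. A reader might infer that both the week-4 and week-8 scores are usually lost. Under an end-of-week review, even 50% attendance is picked up only when the week-4 assessment is due.

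Finally, the direct clash is shown for attendance only. For noncompliance and adverse events it follows from the general rules on safety, estimand and analysis set. For major deviation, the outside-therapy rule is specific, but the article does not say whether such therapy counts as major. A reader might extend the criticism to the grounds on incomplete key assessments and on data integrity. No contradiction is shown for those, and recasting them would be largely preference.

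**Conclusion.** The point holds as a minor one. A discretionary rule allows participants to leave the study on a ground that other sections treat as a per-protocol exclusion with intention-to-treat retention, and the treatment-policy estimand needs their week-8 scores.

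The bias is probably small: about 0.01 to 0.06 SD under moderate assumptions, against a standard error of 0.192 SD. The 0.089 SD case needs 8 of 54 losses to be excess in one group, all benefit lost and no week-4 score. A reader might take it as an upper limit, but it is not a strict one, because 15% attrition is an anticipated rate and not a cap. Equal loss with equal shortfall in both groups gives no bias. The shortfall, the excess withdrawal and the correlation are assumptions that the documents neither give nor exclude.

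The study also describes its findings as hypothesis-generating. The case for change rests on a cheap amendment that keeps scores the estimand needs and that the planned checks cannot replace.

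**What to change.** Amend Criteria for Withdrawal as follows.

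- Make attendance under 80% a ground for stopping study treatment only. For consistency with Safety Monitoring, Primary Estimand and the missing-data section, do the same for protocol deviation or noncompliance and for adverse events requiring discontinuation.
- State that the week-4 and week-8 assessments and adverse event recording continue where the participant is able and consents.
- Keep withdrawal of consent as a ground for leaving the study.
- For anyone already withdrawn, report number, group, ground and last assessment. The section already requires withdrawals and reasons to be documented.

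When to stop treatment remains a clinical decision, and the sample size does not change. The cost is a wording amendment and some effort to bring back participants who have stopped treatment. Enrolment began in January 2025, so outcomes of participants already withdrawn may not be recoverable. Data collection runs to December 2027, so the change still protects later participants. It will not remove losses from withdrawn consent, which are part of the anticipated 15%.
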